**Exclusion criteria:**

- 1) Patients <18 years old
- 2) Comorbid dermatological pathologies that can alter the visualization of the lesions in RCM, such as extensive hyperkeratotic skin diseases or widespread eczema.
- 3) Physiological, general pathological or psychiatric conditions that prevent the patient from being able to lie down for at least 10 minutes (time of RCM evaluation)
- 4) lesions with alterations (ulceration, crust, hyperkeratosis) which prevent RCM visualization.

Additionally, in a smaller population of patients classified at high risk of melanoma, will be evaluated with a total body examination with the RCM (VivaScope 3000) for each melanocytic skin lesion in addition to classic videomicroscopy. Suspected lesions in dermoscopy and / or RCM will be excised. Subsequently, the accuracy of excisions will be compared for both groups, and the benefit of the combined approach to the patient will be calculated. A population of about 300 patients at high risk of developing melanoma (> 100 nevi, > 4 atypical nevi) will be required. These tests will be performed in two of the collaborating outpatient clinics, performed by 2 interchangeable expert specialists (both will examine 50% of the population with dermoscopy and 50% with RCM). Coincident and

discordant data in case of equivocal injury will be compared. Any lesion showing features in dermoscopy and / or confocal that are suspicious of melanoma will be excised. In high-risk patients, any lesions that do not show clear benign features will be routinely monitored with digital videodermoscopy for at least six-months.

The main objective in this case is the quantification of detection of suspected and confirmed malignant lesions on histological examination after excision, with respect to the standard of care (clinical examination + videomicroscopy). The time required for the total-body examination will be measured and compared with a standard videomicroscopy to estimate the cost-benefit value of the procedure.

The previously described statistical tests (chi-square and Z-test) will be applied.

RCM, a non-invasive method performed in vivo, allows an almost histological resolution of skin lesions (*Longo Dermatologia Clin 2012*) used in the standard clinical routine. This method has been used for years in clinical practice at all the collaborating centers. The specific characteristics of melanoma and non-melanoma skin cancer that can be observed with RCM have already been extensively described in literature (*Pellacani JAAD 2005; Pellacani JAAD 2009; Longo Dermatology 2013; Ulrich BJD 2007*).

An increase in diagnostic specificity in skin cancers has already been demonstrated in retrospective studies (*Pellacani JID 2007; Guitera JID 2012*).

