The differences in the frequency of diagnoses obtained in the two study groups will be calculated and compared using the X2 test (chi-square). As a measure of diagnostic efficiency, the NNE (Number Needed to Excise), corresponding to the ratio between malignant lesions and excised benign lesions, obtained in the two different arms, will be calculated. Kolmogorov-Smirnov two-sample Z-test will be used to compare the differences in NNE obtained in the 2 arms. The cost - utility model will be developed in collaboration with the University of Pavia, Department of Pharmacological Sciences, in order to quantify the economic impact on the National Health System.

The model will take into account the costs of treatment (surgery / drug), examination, follow-up visits, devices and histopathology evaluation. The model will be constructed considering two possible alternatives: surgical excision versus RCM examination of equivocal lesions. The model will be tested and adapted based on the real data obtained from the prospective study.

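### The high-risk sub-study pairs both methods within patients and swaps two specialists between them, but its named tests use neither the pairing nor the swap

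*Protocol*

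**What the plan says.** The sub-study is described in the Protocol in the text that follows the exclusion criteria. Its size is given as "A population of about 300 patients at high risk of developing melanoma", with no effect size, alpha or power. Each patient "will be evaluated with a total body examination with the RCM (VivaScope 3000) for each melanocytic skin lesion in addition to classic videomicroscopy", so both methods are applied to the same person. The examinations take place in two clinics and are done by two specialists, described as interchangeable: "both will examine 50% of the population with dermoscopy and 50% with RCM". Most naturally read, this is a reader crossover: in one half of the patients specialist A uses RCM and B dermoscopy, and in the other half the reverse. How patients are put into the two halves is not stated.

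The analysis is one sentence: "The previously described statistical tests (chi-square and Z-test) will be applied". The tests it refers to are in the Statistical analysis section: "The differences in the frequency of diagnoses obtained in the two study groups will be calculated and compared using the X2 test (chi-square", and "Kolmogorov-Smirnov two-sample Z-test will be used to compare the differences in NNE obtained in the 2 arms". The only paired element in the sub-study is that coincident findings and "discordant data in case of equivocal injury will be compared", with no test named. The fields listed under Data collection do not include the examiner, though that list need not be exhaustive.

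**The concern.** The design has two features that the analysis should use. Each patient serves as his or her own control, and the swap balances the two specialists over the two methods. The named tests were written for two separate randomised arms and use neither.

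Three things follow. First, a test for independent groups uses too large a standard error when the two readings on a patient are positively correlated, so power is lost. Second, within any one patient method and specialist are confounded, so a paired test without a specialist term carries the specialist difference as extra noise. Third, the swap cancels a specialist difference only when the halves are equal in size and alike in case mix. Without stated random, balanced assignment, the Protocol does not secure that. If the pairing of specialist and method is not recorded, no later analysis plan can repair it.

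**Working it through.** **Inputs from the Protocol:** about 300 patients, two specialists, each using each method on half of the patients, both methods on every patient, and the two tests named above. The figure of 300 has no stated basis, so there is no calculation to reproduce.

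**Inputs assumed:** a positive finding per patient in 20% with either method (null) or 20% with dermoscopy v 28% with RCM; a reader gap r of 0, 10 or 20 points; a latent within-patient correlation of 0.6 unless noted. Simulations used 4,000 runs per setting.

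**1. Bias.** Let f be the share of patients in whom the specialist who flags more uses dermoscopy. The RCM-minus-dermoscopy difference is δ − r in that share and δ + r in the rest. The pooled mean is δ − r·f + r·(1 − f) = δ + r(1 − 2f).
- f = 0.5: the bias is 0 for any r.
- f = 0.6 (180/120): the bias is −1, −2 or −4 points for r = 5, 10 or 20 points.

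**2. Standard error at an exact 150/150 split.** The equal-weight average of the two halves is the same number as the pooled patient mean; only the variance changes. The pooled per-patient variance equals the within-half variance plus r².
- r = 0.20, null: the simulated SE is 0.0263, so the within-half variance is 300 × 0.0263² = 0.2075. Adding 0.04 gives 0.2475. The removable share is 0.04/0.2475 = 16%.
- r = 0.10, null: 300 × 0.0262² = 0.2059. Adding 0.01 gives 0.2159. The removable share is 4.6%.

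**3. Power for 20% v 28%, 150/150 split.**

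| Reader gap | Unpaired chi-square | Paired, reader ignored | Paired, stratified |
|---|---|---|---|
| 0 | 66% | 83% | 83% |
| 10 points | 67% | 82% | 83% |
| 20 points | 66% | 77% | 82% |

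Hand check of the first row: the chi-square assumes an SE of √(2 × 0.24 × 0.76/300) = 0.0349, while the true SE is 0.0273. Power is Φ((0.08 − 1.96 × 0.0349)/0.0273) = Φ(0.43) ≈ 67%. The paired test has Φ(0.08/0.0273 − 1.96) = Φ(0.97) ≈ 83%. With zero correlation and no gap, all three tests have about 64%, so the gain from pairing depends on the correlation.

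**4. Rejection of a true null at nominal 5%** (ranges cover correlations 0 and 0.6).

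| Split, reader gap | Unpaired chi-square | Paired, reader ignored | Paired, stratified |
|---|---|---|---|
| 150/150, 20 points | 1–5% | 3–4% | 5–6% |
| 180/120, 10 points | 5–9% | 9–12% | 5% |
| 180/120, 20 points | 19–24% | 22–27% | 5% |

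**5. Counts of lesions per patient.** Assume on average one RCM-only and one dermoscopy-only call per patient, with gamma-distributed patient burden (shape 0.5 to 2).
- At 150/150, stratifying a patient-level test cuts the variance by about 7%, 13–17% or 20–29% when one specialist flags 1.5, 2 or 3 times as often as the other.
- Power for a 30% method effect (shape 1) rises from 81% to 86% at ratio 2 and from 66% to 78% at ratio 3.
- At 180/120 and ratio 2, the unstratified paired test rejects a true null in 26% of trials and the stratified one in 5%.

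**The case against.** **The swap already deals with the specialists.** On average it does. A reader might infer that a specialist difference leaks into the RCM comparison even under the stated 50:50 swap. Step 1 shows that it does not: at f = 0.5 the expected bias of the patient-level difference is zero, and stratifying leaves the estimate unchanged. What remains at an exact split is noise.

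**The planned test would reject too often.** A reader might also infer this, because lesions cluster in a few patients. In the count model, rejection rates of 6–11% (reader ratio 2) and 7–15% (ratio 3) at an equal split belong to a pooled paired test on lesions. The Protocol names no such test and does not fix the lesion as the unit here. In the same model, an unpaired chi-square on patients with at least one call rejects in about 1–3% of null trials, so it is conservative.

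**Melanoma counts.** If 10 melanomas fall 7:3 between the halves and the specialists' sensitivities are 95% and 75%, the pooled sensitivity difference is 0.7 × 0.20 − 0.3 × 0.20 = 8 points. This is not a systematic bias. It is 0.8 of one melanoma, and a split of 7:3 or worse occurs with probability 34% under a fair split, equally often in either direction. Taking the patient as unit does not remove it either (1.4 − 0.6 = 0.8 melanoma remains).

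**This is detail for an analysis plan.** A reader covariate alone might be. But the Protocol names the tests, and they are of the wrong kind for paired data.

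**The specialists are called interchangeable, and the layout is partly inferred.** Both are fair points. A small reader gap makes the specialist part of the loss small, but not the pairing part. The text also speaks of comparing both groups, which could suggest separate samples. However, RCM is added to videomicroscopy in the same patient, and coincident and discordant findings can exist only if both methods are applied to the same lesions. Whether one pair of specialists serves both clinics is not stated.

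**Conclusion.** The concern holds in a limited form. The named tests do not match a design in which both methods are used on each patient and two specialists swap between them. The larger cost is from ignoring the pairing: about 16 to 17 points of power under the assumed rates and a correlation of 0.6. Ignoring the specialist adds a modest loss at an exact 50:50 split: about 1 point of power at a 10-point gap and 5 at a 20-point gap. Under an equal split and like halves, a specialist difference does not bias the patient-level comparison on average. It does so if the split is unequal (2 to 4 points at 60:40 with gaps of 10 to 20 points) or the case mix differs. The Protocol does not rule this out, because it states no random assignment of the swap. All sizes rest on assumed finding rates, correlation, reader gaps and lesion burden, none of which the Protocol gives.

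**What to change.** 1. Record for each patient which specialist used which method.
2. State that the two reader-method pairings are assigned at random and in balance, within clinic if the pair of specialists differs between clinics.
3. Replace the sentence that carries over the main trial's tests with a within-patient comparison, with the patient as unit or cluster. Estimate the RCM-minus-dermoscopy difference within each half, average the halves with equal weight, and take the variance within halves. A within-patient model with specialist as a factor can serve the same purpose. Use this for suspicious calls, benign excisions and examination time.
4. For melanoma sensitivity, take the difference in sensitivity within each half, with histologically confirmed melanomas as denominator, and average the two. In the 7:3 example this gives (+20 − 20)/2 = 0 points.

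The cost is one extra data field, an allocation list and slightly more analysis work, with no extra patients or procedures. For the few melanomas expected, stratifying gains little or no precision.

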### **Data collection**

Patients will be coded on the basis of a code generated for each patient enrolled which includes 2 letters (indicating city of enrollment) and 4 consecutive digits (in order of enrolment). In case of multiple lesions for a single patient, lesions will be assigned a letter (A, B, C etc). Essential clinical information for each patient will be collected on an EXCEL file (Gender, age, phototype, number of nevi, number of atypical nevi, family and / or personal history of melanoma, clinical signs of photodamage). For each lesion, the outcome decided during the visit (excision, follow-up) will be indicated. In the event of a lesion referred for follow-up, the subsequent Clinicians' decision (no further follow-up, further follow-up or excision) will be noted.

In the case of excision, upon histological referral, a coded diagnosis will be entered for all the major diagnostic categories. A different EXCEL file, stored on a separate hard-disk and not connected to an external internet network, will collect the code assigned to the patient, the patient's personal data, the date of the visit, any date on which the follow-up is planned / scheduled and personal contact information (telephone / email, etc.) useful for contacting the patient in case the patient does not present for the scheduled follow-up visit. The images coded as described above, without being able to recognize the patient, will be collected on a local Server, with exclusive access allowed by the investigators, through a personal password.

Image management: the images obtained will be coded on the basis of the code generated for each patient enrolled. The images will be stored on local systems (at each individual collaborating center).

Missing data management: any eventual loss of participation by patients' refusal to participate in the study and generated by the randomization process will be compensated the following week, to assure that the number of the patients within both study groups meet the planned dimensions. In case of patients' refusal for surgical intervention, the subject will remain in the study and be monitored over time with a digital follow-up (routine

clinical practice in the case of patients who refuse intervention for lesions without significant suspicion of malignancy), in order to identify lesion modifications, such as increased suspicion of malignancy, enabling a strong recommendation for lesion excision.

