### **Design and description of the study**

This is a prospective randomized 2-arm study (performed in 3 hospitals). Consecutive patients with at least 1 lesion suspicious of melanoma (following clinical and dermoscopy evaluation) will be enrolled. Patients will be randomized to the standard therapeutical care ("Clinical and dermoscopy evaluation only") or standard therapeutical care + RCM integration ("RCM evaluation + clinical and dermoscopy evaluation") following identification of a suspicious lesion during the standard therapeutical care.

The main objective is to evaluate the safety of the integration of RCM (diagnostic identification of melanomas) and cost-effectiveness in terms of the comparison of the number of excisions needed to identify 1 melanoma (including the follow-up period). A cost-utility model will be developed to quantify the impact of the proposed triage system on health care costs and diagnostic effectiveness. This model will be tested on the study population.

Patients will be selected consecutively among patients with suspected skin cancer.

Randomization will be allocated at a 1:1 ratio and patients will be allocated to the “RCM evaluation + clinical and dermoscopy evaluation” or “Clinical and dermoscopic evaluation only” following standard therapeutic care; patients allocated to “Clinical and dermoscopic evaluation only” will likely require immediate biopsy for diagnosis, whereas clinicians of patients allocated to the “RCM evaluation + clinical and dermoscopy evaluation” can decide based on RCM evaluation whether to excise the lesion or refer the patient to subsequent digital follow up. Lesions referred to follow-up will be monitored for at least 6 months, and excised if significant changes are observed on dermoscopy.

In detail, the therapeutic-diagnostic pathway for each study arm are as follows:

a) "RCM evaluation + clinical and dermoscopy evaluation": following routine therapeutic care (clinical-dermoscopic examinations) clinicians of patients with suspicious lesions (at least one major or minor clinical and / or dermoscopic criterion for malignancy, as per inclusion / exclusion criteria) will be able to evaluate the lesions with RCM. A clinical decision (removal or digital dermoscopic follow-up) will be made based on the RCM evaluation.

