b) "Clinical and dermoscopic evaluation only": following routine therapeutic care (clinical-dermoscopic examinations) clinicians of patients with suspicious lesions (at least one major or minor clinical and / or dermoscopic criterion for malignancy, as per inclusion / exclusion criteria), will make a clinical decision (removal or digital dermoscopic follow-up) without RCM evaluation.

Each participating center will be responsible for its own case history and clinical decisions. Each center will take care of the collection and storage of data. At interim analysis (18 months) collected data and preliminary results will be evaluated collectively and discussed. The investigators at the participating centers have high-level therapeutic-diagnostic pathways in place, as documented by the numerous publications produced by these centers, however, in case of significant discrepancies among the interim clinical performance data, or if requested by individual investigators, some cases may be evaluated independently by other investigators in order to verify diagnostic agreement. These cases may derive either from direct indications from the investigators or randomly selected from the collected cases.

Images will be anonymized and only essential clinical data (sex / age, any significant present or past pathologies) will be provided to the other evaluators.

The definition of the head / neck lesion subset is as follows:

1. Malignant macules with histological diagnosis of melanoma;
2. Benign macules with histological diagnosis of actinic keratoses, solar lentigos, lichen planus-like keratosis, seborrheic keratoses, freckles and junctional / compound / dermal nevi;
3. Benign macules not subjected to biopsy and with clear and defined parameters of clinical, dermoscopic and confocal microscopy benignity;

The main outcome will be the rate of malignant lesions identified within the "RCM evaluation + clinical and dermoscopy evaluation" compared to "Clinical and dermoscopic evaluation only" study arms.

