**Inclusion criteria:**

- 1) Adult patients (18-90 years) referred to the Dermatology departments of the collaborating centers.
- 2) Patients able to give consent to participate
- 3) Patients with at least 1 lesion with at least one major or minor clinical and / or dermoscopic criterion of suspicion of malignant tumor lesion (Friedman 1987; Argenziano 2002) identified during the clinical and dermoscopy evaluation.
- 4) Willingness to participate in the study and able to give written informed consent

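### Patients are randomised but outcomes are recorded and partly counted per lesion; the protocol names tests for independent observations without stating the unit of analysis or handling within-patient correlation

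*Protocol*

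**What the plan says.** **Randomised unit.** Design and description of the study: "Patients will be randomized to the standard therapeutical care" or to standard care plus RCM, and "Randomization will be allocated at a 1:1 ratio". The power calculation under Statistical analysis is in subjects (532), inflated to at least 2375 patients.

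**Observed unit.** Inclusion criterion 3 admits "Patients with at least 1 lesion with at least one major or minor clinical" or dermoscopic criterion of suspicion, with no upper limit on lesions. Data collection provides for several lesions per patient: "In case of multiple lesions for a single patient, lesions will be assigned a letter (A, B, C etc". It adds: "For each lesion, the outcome decided during the visit (excision, follow-up) will be indicated". Each excision then receives a coded histological diagnosis.

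**Outcomes.** For the head/neck subset, "The main outcome will be the rate of malignant lesions identified within the" RCM arm, compared with the control arm. NNE is defined as "corresponding to the ratio between malignant lesions and excised benign lesions".

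**Tests.** Statistical analysis: "The differences in the frequency of diagnoses obtained in the two study groups will be calculated and compared using the X2 test (chi-square"). NNE is assigned to a two-sample Kolmogorov-Smirnov test. The text on the high-risk sub-study, which follows the exclusion criteria, applies the same two tests there.

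The protocol defines no index lesion, no patient-level endpoint and no method that allows for several lesions from one patient.

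**The concern.** Arm is constant within a patient, so all lesions of one patient fall in the same arm. They also share the patient-level characteristics that the protocol itself collects: phototype, nevus count, atypical nevi, melanoma history and photodamage. Positive correlation between lesions of one patient is therefore plausible. It makes the variance of a between-arm difference in lesion proportions larger than the chi-square test assumes. The test then rejects a true null hypothesis more often than 5%, and intervals computed as if lesions were independent are too narrow.

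This is more than a detail left to a statistical analysis plan. The protocol names the tests, and an analysis plan that followed it faithfully would carry the problem forward.

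**Working it through.** **1. The protocol's own sample size.** Inputs from Statistical analysis: 7.3% against 14%, power 80%, alpha 0.05 (sidedness not stated), 1:1. Formula per arm:

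n = [z_a √(2p̄(1−p̄)) + z_b √(p1(1−p1) + p2(1−p2))]² / (p2−p1)², with p̄ = 0.1065.

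- One-sided: (1.645 × 0.4363 + 0.8416 × 0.4337)² / 0.067² = 262 per arm, 524 in total, which is within 3% of the stated 532.
- Two-sided: 332 per arm, 664 in total.
- Inflation: 532 / 0.224 = 2375, as stated.

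The sidedness is a separate matter. What counts here is that the formula takes one independent observation per subject.

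**2. Effect of clustering on the chi-square test, if lesions are the unit.** With m lesions per patient (equal numbers) and within-patient correlation ICC:

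- design effect DE = 1 + (m−1) × ICC
- true two-sided type I error = 2 × [1 − Φ(1.96/√DE)]
- an independence-based 95% interval should be wider by the factor √DE

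The protocol gives neither m nor ICC. The values below are assumptions.

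| m | ICC | DE | True error at nominal 5% | √DE |
|---|---|---|---|---|
| 1.1 | 0.05 | 1.005 | 5.1% | 1.002 |
| 1.1 | 0.3 | 1.03 | 5.4% | 1.015 |
| 1.5 | 0.1 | 1.05 | 5.6% | 1.025 |
| 1.5 | 0.3 | 1.15 | 6.8% | 1.072 |
| 2 | 0.1 | 1.10 | 6.2% | 1.049 |
| 2 | 0.3 | 1.30 | 8.6% | 1.140 |
| 3 | 0.3 | 1.60 | 12.1% | 1.265 |

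**3. Unequal numbers of lesions.** In practice most patients would have one lesion and a few would have several. This was simulated with a beta-binomial model: 266 patients per arm, a common rate of 10.65%, 20,000 runs and a plain chi-square test on lesions. With a mean of 1.25 lesions, the error was 5.7% (ICC 0.1) and 6.6% (ICC 0.3). With a mean of 2.0, it was 7.1% and 11.7%. The last figure exceeds the 8.6% in the table because patients with many lesions weigh more.

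**4. Power.** Clustering does not undermine the number of subjects. At m = 3 and ICC 0.3, the 532 subjects would supply 532 × 3 = 1596 lesions, worth 1596/1.6 = 997.5 independent ones. That is more than 532. The harm lies in the error rate and in interval coverage.

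**The case against.** The strongest reply is that the chi-square sentence names neither lesions nor patients. The power calculation beside it is in subjects, and the same section equates 800 patients with 400 cases per arm. If each patient is counted once, then randomisation, sample size and test share one unit and the chi-square test is valid. This stands in part: a reader might infer that the main test is certainly run on lesions and certainly exceeds 5%, and the text does not establish that. But the patient reading is not stated either. It would need a rule for patients with several lesions, which the protocol lacks, and the outcomes it does define (NNE, rate of malignant lesions) are in lesions.

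Four further limits also stand.

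- **NNE** goes to the Kolmogorov-Smirnov test, so the chi-square calculation above does not measure the error of the NNE comparison. That test assumes independent observations too.
- **Intervals.** A reader might infer that all intervals for sensitivity, specificity and odds ratios are too narrow. The protocol does not say how they are computed, so this follows only for standard independent-observation methods.
- **Size.** Three lesions per patient with ICC 0.5 would give DE 2.0 and an error of 16.6%. At the protocol's 7.3% rate, however, that correlation means a second lesion has a 0.073 + 0.5 × 0.927 = 54% chance of being melanoma once the first is. Nothing in the document supports that.
- **High-risk sub-study.** Lesions there appear to be assessed by both dermoscopy and RCM. An unpaired test on paired data can err on the conservative side, so the direction of error is uncertain.

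**Conclusion.** The point holds in conditional form. The protocol combines patient randomisation, several lesions per patient, lesion-count outcomes and tests for independent observations. It neither names the unit of the chi-square test nor provides for within-patient correlation. If lesions are the unit and are positively correlated, the between-arm test is anti-conservative. Over the equal-size grid, the true error runs from about 5.1% to about 12%, with 8.6% at two lesions per patient and ICC 0.3. These figures rest wholly on assumed lesion numbers and correlations, and the effect is negligible if nearly all patients contribute one lesion. In the high-risk sub-study, clustering is hard to avoid because each melanocytic lesion is examined in patients selected for more than 100 nevi or more than 4 atypical nevi. With pairing also in play, all that can be said is that the carried-over tests do not fit the data structure. The change should be made before analysis, but the point does not show that the trial's main result will be wrong.

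**What to change.** In Statistical analysis:

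- State that the patient is the unit of the primary chi-square comparison, with a one-line endpoint such as at least one melanoma diagnosed. This matches the sample size in subjects. Confirm that 7.3% and 14% are meant as percentages of patients.
- Analyse lesion-level outcomes with GEE or a cluster-robust variance, clustered on patient.
- Obtain intervals for NNE, sensitivity and specificity by resampling patients. Use the same patient-level bootstrap for the between-arm NNE comparison, in place of the Kolmogorov-Smirnov test.

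In the high-risk sub-study, replace the carried-over tests by a method that respects both the pairing of the two examinations and the clustering of lesions within patient.

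Report the distribution of lesions per patient by arm, so that readers can see how much the adjustment matters.

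The cost is an endpoint definition, revised analysis wording and somewhat wider lesion-level intervals (up to about 26% wider at three lesions and ICC 0.3, hardly at all near one lesion per patient). No new data are needed, because the patient code and lesion letter are already recorded. Recruitment, visits and clinical decisions are unaffected.
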